### 1) Antiviral therapy

In the HBsAg (+) group, antiviral therapy will be initiated if HBV-DNA levels are greater than 200,000 IU/mL at gestational weeks 24–28 until delivery. During the antiviral treatment, subjects who confirm CLCr < 50ml/min will receive the adjusted dose of the study drug based on the renal function and be monitored closely at 4-week intervals.

### 2) Infant immunization

All newborns from HBsAg (+) pregnant women will receive hepatitis B immunoglobulin (HBIG,100IU) with the first dose of the hepatitis B vaccine (10 µ g) within 12 h after birth. The second and third injections of the hepatitis B vaccine will be administrated intramuscularly at the age of 1 month and 6 months, respectively. For all healthy pregnant women, their newborns will receive the same hepatitis B immunoprophylaxis regimen and schedule without the birth dose of HBIG for infants.

.

### Laboratory assessments

Laboratory tests will include the following: liver function and biochemistry, HBV serological testing, HBV DNA, and HBV genotype. The imaging tests will include transient elastography (TE) and sonogram. We also assess the HBV virus mutation including pre-S, BCP, and PC.

### Study endpoints

The primary endpoints are the proportion of HBsAg (+) pregnant women with elevated ALT within 24 weeks postpartum and the frequency of persistently elevated ALT for more than 12 weeks in HBsAg (+) pregnant women. Secondary endpoints include the proportion, peak, and period of ALT elevation in healthy pregnant women within 24 weeks postpartum; and the comparison of the secondary endpoints between the HBsAg (+) pregnant women group and healthy pregnant women group.

### Data collection

The following variables at the baseline will be collected:

Age.BMI.History of hepatitis B.Reproductive history.Complication.Drugs that have previously been taken.Baseline laboratory data: including total bilirubin, ALT, aspartate transaminase (AST), and TE. In addition, HBsAg, HBsAb, HBeAg, HBeAb, HBcAb, HBV DNA, genotype, pre-S, BCP, and PC were detected in HBsAg (+) group.

The subsequent data collection during follow-up visits is presented in Table 1.

**Table 1 Tab1:** Patient follow-up schedule and data collection

Visit(week)	12–20	Baseline(20–24)	28	32	36	delivery	4–8	12	24
Confirm eligibility	√	√							
Seek informed consent	√								
Medication review	√								
Medical history collection	√	√	√	√	√	√	√	√	√
Physical examination	√	√	√	√	√	√	√	√	√
Fetal ultrasound results	√								
Hematology laboratory tests	√	√	√	√	√	√	√	√	√
TE tests	√	√				√	√	√	√
Detection of HBV Virus Genetic Characteristics		√				√			√
Adverse Event Evaluation		√	√	√	√	√			
Weight management, dietary guidance	√								
Fetal physical examination						√			
Combined immunization						√			

Blood tests include a chemistry profile and HBV serological testing (HBsAg, HBsAb, HBeAg, HBeAb, and HBcAb) along with the HBV DNA levels. The detection of HBV viral genetic mutations includes pre-S, BCP, and PC.

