**Method:**

This study is a single-center and prospective cohort study (n = 360) that consists of two groups of patients including HBsAg-positive mothers (n = 120) and healthy mothers without HBV infection (n = 240). In HBeAg-positive mothers, antiviral therapy during late pregnancy is permitted to prevent Mother-to-child transmission (MTCT) but discontinued at delivery if there is no further indication for the treatment. Mothers are enrolled at the gestational weeks of 12–24. After delivery, both mothers and their infants will be followed up until postpartum week 24. Clinical and laboratory data are collected every 4 weeks during the study except there are no follow-up visits at the postpartum weeks 16 and 20. The primary objective is the proportion of patients with postpartum ALT flares. The secondary objectives are independent risk factors during pregnancy for predicting postpartum ALT flares and the normal range of postpartum ALT levels in healthy mothers.

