In young mothers with hepatitis B infection and high viral load without significant hepatitis, postpartum disease activation or hepatitis flare has been reported in the range of 15-35% [7, 8]. In a multicenter and prospective randomized controlled trial (RCT), Pan et al. observed that postpartum ALT elevation occurs in both mothers who were treated with tenofovir disoproxil fumarate (TDF) or received no therapy during pregnancy (45% vs. 30%) [9]. Another prospective study also showed that 36.3% of pregnant women who received antiviral therapy during pregnancy had postpartum hepatitis flares. Some of the ALT flares might further progress to acute exacerbation of hepatitis or even hepatic decompensation without timely antiviral treatment [7, 8]. In mothers without antiviral treatment during pregnancy, a large retrospective cohort study with 4236 hepatitis B mothers in China found that the postpartum ALT elevation rate was 28.27% [9]. Several independent predictors for postpartum ALT elevations were found in this subpopulation, which included high viral load or elevated transaminase during pregnancy. The peak period of ALT flares occurred between postpartum weeks 4–6 and weeks 9–12, with a bimodal distribution [9]. However, the study noted several limitations, including the lack of data on maternal virological features such as genotype, basal core promoter, pre-core mutation, and pre-S mutant. In addition, the postpartum follow-ups were within 12 weeks in most mothers. In chronic hepatitis B patients at the immune tolerance phase, basal Core Promoters (BCP) and pre-core (PC) mutations are common in HBeAg-positive patients (up to 60%) and have been linked to immune activation [10, 11]. Recently, a study by Luo et al. [12] suggests that the mutations of PC and BCP in HBeAg-positive pregnant women during antepartum could predict spontaneous HBeAg seroconversion after delivery. However, the postpartum elevation of ALT or hepatitis B flares has not been clearly described and analyzed.

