### Recruitment

Subjects will be recruited through the Department of Infectious Diseases and Obstetrics Clinic of the Fifth Affiliated Hospital of Guangzhou Medical University. Recruitment began in June 2022. Based on the published literature [7, 9, 15] the frequency of elevation ALT in HBV-infected pregnant women during the postpartum period is estimated at the range of 11.6–30.6%. We calculate the sample size for the current study (presume p = 26%, q = 10%, type I error α = 0.05, test efficiency 1-β = 0.9) in the HBsAg (+) group and set the number of patients to approximately 120. In the healthy mother group, 240 subjects are planned to be enrolled (HBV mothers: healthy mothers at the 1:2 ratio). The total of subjects in the study will be 360. We estimate about 5-10% of subjects may withdraw from the study. The total number of patients who have completed data at the end of the study will be 108 in the HBsAg (+) group and 216 in the healthy pregnant women group, respectively. The sample size will provide enough to observe the adverse events with an incidence of 3% or greater.

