### Trial intervention

Although our study is observational, due to the compliance with the practice guidelines recommended by the national professional association, mothers with high levels of HBV viremia will receive antiviral treatment during pregnancy and all infants will receive HBIG and HBV vaccines. These medical products are independently prescribed for participants in the study and are part of a standard care treatment strategy, which is not determined in advance by our research protocol. These treatments are applied based on clinical practice. However, we will assess the safety of mothers and newborns who receive the intervention. There will not be trial-specific intervention implemented in the study.

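### Table 1 schedules no adverse-event evaluation after delivery, although the protocol promises a safety assessment of mothers and newborns and follows both to postpartum week 24

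*Protocol article*

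**What the plan says.** The Data collection section makes Table 1 the schedule: "The subsequent data collection during follow-up visits is presented in Table 1". In that table the row "Adverse Event Evaluation" is ticked at baseline (20–24 weeks), at 28, 32 and 36 weeks, and at delivery. It is blank at the first column (12–20 weeks) and at postpartum 4–8, 12 and 24 weeks.

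Other parts of the same article point past delivery:

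- Abstract, Method: "both mothers and their infants will be followed up until postpartum week 24".
- Trial intervention: treatments are standard care, but "we will assess the safety of mothers and newborns who receive the intervention". The care described there is antivirals for highly viremic mothers, and HBIG and vaccine for infants.
- Abstract, Method, on antivirals: "discontinued at delivery if there is no further indication for the treatment". The Antiviral therapy section likewise runs treatment until delivery.
- Infant immunization: HBIG (HBsAg-positive mothers only) and the first vaccine dose within 12 hours of birth, then vaccine at 1 and 6 months.
- Background: "Some of the ALT flares might further progress to acute exacerbation of hepatitis or even hepatic decompensation without timely antiviral treatment".
- Recruitment: "The sample size will provide enough to observe the adverse events with an incidence of 3% or greater".

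**The concern.** The adverse-event row ends where two of the exposures of interest change. For treated mothers, delivery is when the antiviral may be stopped, and the Background names exacerbation and decompensation as possible consequences of postpartum flares. For infants, delivery is when exposure to HBIG and vaccine starts. A safety assessment of mothers and newborns who receive this care needs data from after that point, and the table schedules no evaluation there.

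At stake is how a postpartum safety result can be read. If adverse events are actively sought at five visits up to delivery and at none afterwards, a low count after delivery cannot be separated from a lower intensity of looking. Events not recorded prospectively are also hard to reconstruct later.

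**Working it through.** **Step 1. The schedule, counted from Table 1.** There are six columns up to and including delivery, and three postpartum columns.

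| Row | Ticks up to delivery (of 6) | Ticks postpartum (of 3) |
|---|---|---|
| Adverse-event evaluation | 5 | 0 |
| Medical history | 6 | 3 |
| Physical examination | 6 | 3 |
| Blood tests | 6 | 3 |
| Transient elastography (TE) | 3 | 3 |
| Fetal physical examination | 1 (delivery) | 0 |
| Combined immunization | 1 (delivery) | 0 |

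The adverse-event row has all nine cells, and the rows for history, examination and blood tests are ticked in all nine. The blanks are therefore a feature of the schedule and not a broken table.

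**Step 2. What this leaves for mothers.** The Study endpoints section defines the primary endpoints as ALT elevation within 24 weeks postpartum and its persistence beyond 12 weeks. With blood tests at 3 of 3 postpartum visits, ALT flares are measured. The endpoints listed there concern ALT only. Decompensation, hospital admission and other non-ALT events are not endpoints, and they have an adverse-event evaluation at 0 of 3 postpartum visits. They could surface only through history, examination or laboratory review.

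**Step 3. What this leaves for infants.** The delivery tick could catch events at birth. After that, no row in Table 1 is specific to the infant. The 1-month vaccine dose falls near the 4–8 week visit, which has no tick. The 6-month dose is nominally at 6 × 365/12 = 182.5 days, against 24 × 7 = 168 days for the last visit, so it falls about two weeks after follow-up ends.

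**Step 4. The 3% statement in Recruitment.** The plan's own figure is checked first. The chance of at least one event at true incidence 3% among n mothers is 1 − 0.97^n.

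- 108 HBsAg-positive completers (120 × 0.9): 1 − 0.97^108 = 0.963.
- 120 enrolled: 1 − 0.97^120 = 0.974.
- 324 completers in both groups (108 + 216): above 0.999.
- Smallest incidence seen with 95% probability in 108: 1 − 0.05^(1/108) = 2.7%.

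The figure is sound for the HBsAg-positive group and for the whole sample. The sentence does not say to which population or period it applies. The binomial calculation assumes that events are looked for throughout the period meant, which Table 1 provides up to delivery only.

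**The case against.** The strongest reply has four parts.

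- *The mothers are still seen.* History, examination, chemistry, HBV DNA and TE continue at every postpartum visit, and the flare after antiviral stop is what the study is built to measure. This stands. A reader might infer from the blank cells that postpartum maternal events are not collected, or that serious hepatic events would be missed. The documents do not support that. What is absent is a scheduled adverse-event evaluation at visits that already include clinical and laboratory review.
- *The row matches the treatment period.* The ticks run from baseline to delivery and so cover the antiviral course, and the study is observational, with no safety endpoint among its primary or secondary endpoints. This is true and limits the weight of the point. It does not answer the newborn half of the safety statement, because infant exposure only begins at delivery.
- *Table 1 is visibly not a full infant schedule.* It ticks immunization at delivery only, although doses at 1 and 6 months are planned, and a fuller schedule may sit in the full protocol. This partly stands: a blank cell does not prove that no infant data are taken. But the article presents the table as its follow-up schedule, and as printed it conflicts with the article's own text.
- *The 3% figure is right.* This stands. A reader might infer that it fails for treated mothers, since entry requires HBV DNA above 2,000 IU/mL while "antiviral therapy will be initiated if HBV-DNA levels are greater than 200,000 IU/mL", so the treated may be a subset. But the Recruitment section makes no claim about treated mothers, the number treated is not given, and no detection probability is stated. If 95% were adopted, the requirement would be ln(0.05)/ln(0.97) = 98.4, or 99 treated mothers. Whether the study falls short of that cannot be established from the documents.

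**Conclusion.** The point holds as an internal contradiction. Table 1 schedules adverse-event evaluation at 0 of 3 postpartum visits, while the Trial intervention section promises a safety assessment of mothers and newborns and the Abstract follows both to week 24. The gap is widest for infants, whose exposure begins as evaluation ends. For mothers it concerns non-ALT events. ALT flares and the primary endpoints are unaffected.

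The consequence is limited but real: a low postpartum adverse-event count could reflect the schedule. How many events might go unrecorded cannot be estimated from the documents. The conclusion assumes that Table 1, as printed, is the schedule the site follows. The 3% statement is not in error. It lacks only a population and a period.

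**What to change.** Reconcile Table 1 with the Abstract and the Trial intervention section:

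1. Tick the adverse-event row at postpartum 4–8, 12 and 24 weeks, and state that it covers both mother and infant. The Abstract and the Research scheme section word the postpartum visits differently; the row should follow whichever visits are kept.
2. State whether events after the 6-month vaccine dose are meant to be covered, since that dose nominally falls after the week-24 visit.
3. Recruitment began in June 2022. For participants already past a postpartum visit, mark events taken from the records as retrospective.
4. Optionally, add to the Recruitment sentence, for example: with 108 HBsAg-positive completers there is a 96% chance of seeing at least one event of 3% incidence, over a named period.

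The cost is three table cells and extra recording at visits the mothers already attend. For infants it assumes that they attend with the mother or that she reports for them. Sample size, endpoints and the main analyses do not change.

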### Data management

Patient-derived metadata will be de-identified and uploaded to a research database with privacy protection. Once uploaded it will not be possible to alter the data. Only the PI and research associate of the current project will have access to data.

### Patient and public involvement

Patients or the public are not involved in the current study’s design, conduct, reporting, or dissemination plans.

### Statistical methods

The statistical analyses will be performed with SPSS 23.0 version (IBM, New York, USA) statistical analysis software. Demographic and baseline measurements will be summarized using standard descriptive methods and stratified by the study groups. Baseline data for mothers will include a summary of previous gravidity, log10 HBV DNA levels, and ALT levels. The baseline data for infants will include a summary of body weight, height, head circumference, gestational age, delivery mode (cesarean section vs. virginal delivery), Apgar score, HBsAg positivity at birth, and HBeAg positivity at birth. The aforementioned baseline variables between the two groups of ALT elevation and ALT normal after delivery. The quantitative data will be summarized with a mean (SD) or median (range), and the differences between groups will be compared by a student’s t-test. The categorical data will be presented with counts or percentages and compared by the chi-square or non-parametric tests. Further analysis of predictors for ALT flares will be conducted by multivariate analysis in HBsAg positive pregnant and the area under the ROC curve will be used to predict ALT rise. A mixed linear model will be established by repeated measurement and missing value analysis to analyze the changing trend of ALT after delivery. A nested case-control study will be used to analyze the baseline risk factors for elevated ALT (further subgroup analysis of mild and severe elevated ALT). We consider the results to be statistically significant differences when the P value is < 0.05.

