### Strengths and limitations of the study

This study is to investigate the frequency and severity of postpartum ALT flares in chronic hepatitis mothers, which have been reported with inconsistency in published studies.We also investigate the postpartum ALT changes in mothers without hepatitis B and explore the normal range of ALT, which has not been clearly defined in this subpopulation.Our data will clarify the maternal independent risk factors during pregnancy for predicting postpartum ALT flares in mothers with chronic hepatitis B through multivariate analyses.The study also compares the frequency and features of postpartum ALT flares between HBeAg-positive mothers versus those with HBeAg-negative, providing data for making clinical decisions for further intervention or monitoring based on HBeAg status.Our study inherits the short-coming of the cohort study without randomization and the limitation of short-term patient follow-up. However, our data may provide a road map for future studies.

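### The objective is risk factors during pregnancy, but the two risk-factor analyses that state a time point use baseline, where ALT is normal by eligibility and HBV DNA precedes antiviral therapy

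*Protocol article*

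**What the plan says.** The Abstract (Method) states the aim: "The secondary objectives are independent risk factors during pregnancy for predicting postpartum ALT flares". Strengths and limitations repeats it, promising to "clarify the maternal independent risk factors during pregnancy for predicting postpartum ALT flares" by multivariate analysis.

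Statistical methods describes three analyses that bear on this aim.
- **Comparison by outcome.** "The aforementioned baseline variables between the two groups of ALT elevation and ALT normal after delivery". For mothers the list reads: "Baseline data for mothers will include a summary of previous gravidity, log10 HBV DNA levels, and ALT levels".
- **Nested case-control study.** Its purpose is to "analyze the baseline risk factors for elevated ALT", with a further split into mild and severe elevation.
- **Multivariate analysis with ROC** in HBsAg-positive mothers. No time point is given for the predictors.

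Table 1 labels the visit at 20–24 weeks as baseline. Its blood-test row is ticked again at 28, 32 and 36 weeks and at delivery. The note below the table says that these tests cover chemistry and HBV serology "along with the HBV DNA levels".

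**The concern.** The objective covers the whole of pregnancy, and the data are collected up to delivery. Where the analysis text names a time, however, it names baseline. No maternal value from week 28 to delivery is named as a predictor, and neither is antiviral exposure.

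Two features of this design make the gap matter. Eligibility removes raised ALT from the baseline visit. Antiviral therapy falls between baseline and delivery in mothers with high viral load. If the analysis is carried out as worded, the nested case-control study, which also carries the mild/severe analysis, cannot examine one of the article's own cited predictors, and it would relate flares to a viral load measured before therapy with no term for that therapy.

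**Working it through.** **1. The plan's own figures.** Recruitment assumes 26% versus 10%, α = 0.05 and power 0.9. With two groups of equal size, a two-sided test and pooled variance:

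n = [1.960 × √(2 × 0.18 × 0.82) + 1.282 × √(0.26 × 0.74 + 0.10 × 0.90)]² / 0.16² = (1.065 + 0.681)² / 0.0256 ≈ 119.1, so 120 per group.

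This matches the stated 120. With 10% withdrawal, 120 × 0.9 = 108 completers, also as stated. The present point does not depend on the sample size; 108 is needed only in step 5.

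**2. Predictor windows side by side.**

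| Place | Window |
|---|---|
| Abstract (Method); Strengths and limitations | during pregnancy |
| Comparison by outcome | baseline |
| Nested case-control study | baseline |
| Multivariate analysis and ROC | not stated |
| Table 1, maternal blood tests | 12–20, 20–24 (baseline), 28, 32, 36 weeks, delivery |

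Four scheduled antenatal or delivery readings after baseline (28, 32, 36 weeks, delivery) have no named role as predictors.

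**3. ALT.** The inclusion criteria require two consecutive normal ALT results at least 30 days apart. The exclusion criteria remove anyone whose ALT rose earlier in this pregnancy. Table 1 ticks the eligibility check at both 12–20 and 20–24 weeks. Baseline ALT can therefore vary only within the normal range. Background and Discussion cite raised transaminase in pregnancy as an independent predictor of postpartum elevation. In this cohort such a rise can appear only from week 28 onward.

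**4. HBV DNA.** Baseline is at 20–24 weeks. Under Antiviral therapy, mothers above 200,000 IU/mL start treatment at 24–28 weeks and continue to delivery. For them the baseline value is a pre-treatment value. Background hypothesises that antiviral therapy may influence flare patterns, and Discussion says the effect of stopping it is not fully investigated. No analysis names exposure to it.

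**5. Cost in candidate terms.** Take the plan's rate of elevated ALT as the flare rate.
- At 26%: 108 × 0.26 = 28.1 flares.
- At the cited range of 11.6–30.6%: 108 × 0.116 = 12.5 to 108 × 0.306 = 33.0 flares.

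The article names three maternal baseline variables. Replacing baseline ALT adds no term. Antiviral exposure makes four, and late HBV DNA makes five.

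| Terms | 12.5 flares | 28 flares | 33 flares |
|---|---|---|---|
| 3 | 4.2 per term | 9.3 per term | 11.0 per term |
| 5 | 2.5 per term | 5.6 per term | 6.6 per term |

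These ratios are upper limits, because any other candidate (HBeAg, genotype, viral mutations) lowers them.

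**The case against.** **Not every analysis is tied to baseline.** A reader might infer that the risk-factor work uses baseline values only. The document does not support that. The multivariate and ROC sentence carries no such limit, and Strengths and limitations links the objective to multivariate analysis. That analysis may already be meant to include later values. This stands, and it confines the point to the two analyses that are fixed at baseline.

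**Baseline is used loosely.** The listed baseline variables include infant data known only at birth, such as delivery mode and Apgar score. This also stands. For mothers, though, the only definition is the 20–24 week column of Table 1.

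**Weeks 20–24 are part of pregnancy.** A baseline analysis covers part of the objective and does not contradict it. Agreed: the fault is incomplete coverage.

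**Such detail belongs in the full protocol or analysis plan.** That is a fair answer to the silence of the multivariate sentence, which is not counted as a fault here. It does not answer the other two sentences, which positively say baseline.

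**Pre-treatment viral load may be the right predictor.** A reader might infer that treated mothers are judged on a viral load they no longer have. The document gives neither the treated share nor the fall in HBV DNA on therapy. Therapy also ends at delivery unless still indicated, so the pre-treatment level is not shown to be irrelevant to the weeks that follow. A low value at delivery would mix mothers suppressed by treatment with mothers whose level was low throughout. This objection stands: baseline HBV DNA should be kept and not replaced.

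**Conclusion.** The point holds as a mismatch of limited scope. Two of the three risk-factor analyses are fixed at baseline, while the objective, stated twice, is risk factors during pregnancy. The clearest consequence needs no outside assumption: raised ALT in pregnancy cannot be studied at baseline because eligibility excludes it. For HBV DNA the narrower statement is that the baseline value precedes therapy and that neither therapy nor a later value is named beside it.

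The effect on the study's findings cannot be calculated from what the document gives. The primary endpoints are untouched. It is a worthwhile improvement at low cost, using data already scheduled. The conclusion assumes that the 20–24 week column of Table 1 is the maternal baseline and that the eligibility checks are applied as written.

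**What to change.** In Statistical methods:
1. Replace the word baseline in the nested case-control sentence so that it covers "independent risk factors during pregnancy for predicting postpartum ALT flares", as the objective does.
2. In place of baseline ALT, use one antenatal ALT summary from week 28 to delivery, either the highest or the last value, chosen in advance.
3. Keep baseline (pre-treatment) HBV DNA and add antiviral exposure (yes/no).
4. Pre-specify HBV DNA at 36 weeks or delivery, or its fall from baseline, as an additional predictor. Never pool treated and untreated mothers on delivery HBV DNA without the treatment term.
5. State that the same time points apply to the multivariate and ROC analysis.
6. Keep a baseline-only model as a second analysis.

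The cost is analysis wording, with no new visits or samples. There are three downsides. One or two more candidate terms are spent against about 28 expected flares, so other candidates should be few. Where a late sample is missing, the last available value has to be used. Because treatment is assigned by HBV DNA level, the exposure term will overlap with baseline HBV DNA and should be read as a predictor, not as an estimate of treatment effect.
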